##### Cancer Treatment Cohort

The primary end point is the proportion of those who are adherent to cancer treatment (complete all treatment modalities as prescribed; 2-week delays will be allowed) at 12 months after diagnosis, the secondary end point is the proportion alive at 12 months after diagnosis, and the tertiary end point is the proportion with recurrence at 24 and 36 months (among those with 24- and 36-month follow-up).

For all the AYA living with HIV, we will report adherence to ART (proportion of those filling prescriptions at least every 3 to 6 months) and viral load at 12, 24, and 36 months. Viral load testing is generally conducted at least annually for AYA living with HIV as part of routine guideline-recommended practice. We will reinforce the need for regular viral load testing as part of health care provider training and have set aside funds to conduct viral load testing for study participants for whom this information is unavailable in the medical record.

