##### Cancer Treatment Cohort

We will use stratified random assignments to place patients in each arm of the trial. Once we have enrolled 10 patients with each type of cancer, we will randomly assign half to the ARROW program and the other half to the one-time education arm. All patients will have a minimum of 12 months of follow-up, and some will have up to 36 months of follow-up. Data will be collected at baseline and then annually for the 3-year duration of the trial from the AYA living with HIV through surveys and by abstracting information from the Cancer Diseases Hospital records. The sample size (n=500) was calculated using conventional specifications (α=.05; 2-sided tests) based on the primary end point and allowing for an absolute 15% point improvement; the estimated current level of adherence is 75%, which will increase to at least 90% with the ARROW program. With 50% (250/500) of the patients in each arm, we will have more than 90% power to detect this difference.

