**Data elements for primary, secondary, and tertiary end points: HIV and cancer care continuum**				
	Proportion of participants completing physical examination (KS^a^ and NHL^b^) and up to date with CC^c^ screening	Confirmation of services will be based on clinical records and PC^d^ tracking tool (primary end point at 24 mo)	Biological, imaging, and clinical procedures identified through clinical records and study database	12, 24, and 36 mo
	Proportion of participants completing diagnostic tests and initiating treatment in ≤90 d	Measured as days from referral for testing and cancer diagnosis, respectively; based on chart review and study data	Biological, imaging, and clinical procedures identified through clinical records and study database	24 and 36 mo
	Proportion of participants completing repeat examinations and screening at the recommended interval	Screening every 2 y for CC and annual examination (especially when CD4^e^<100) based on the Zambian guidelines	Biological, imaging, and clinical procedures identified through clinical records and study database	36 mo
	Proportion of participants with early-stage diagnosis^f^	Stage 1 or 2 for NHL and CC; good risk for KS^g^	Biological, imaging, and clinical procedures identified through clinical records and study database	36 mo
	Proportion of participants adherent to cancer treatment^f^	Complete cancer treatment modalities as recommended	Biological, imaging, and clinical procedures identified through clinical records and study database	12 mo after diagnosis
	Proportion of participants alive at 12 mo after diagnosis^f^	Follow-up conducted by PCs and entered in study database	Biological, imaging, and clinical procedures identified through clinical records and study database	12 mo after diagnosis
	Proportion of participants with recurrent disease^f^	AYA^h^ living with HIV and cancer who experience cancer recurrence	Biological, imaging, and clinical procedures identified through clinical records and study database	36 mo
	Proportion of participants adherent to ART^i^ and viral load	Prescription filled every 3 to 6 mo; blood test	Biological, imaging, and clinical procedures identified through clinical records and study database	Annually

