**HIV status, demographics, mediating outcomes, intervention dose, and clinical services**				
	HIV status and diagnosis date	Perinatally or behaviorally infected; CD4 count	Clinic record	Baseline
	Demographics and socioeconomic status	Research Triangle Institute AYA Zambia survey	Self-report	Baseline
	Self-efficacy (AYA living with HIV)	Generalized self-efficacy Scale [69]	Self-report	Baseline and 12, 24, and 36 mo
	Social support and mental health (AYA living with HIV)	Brief social support and patient health questionnaires [69,70]	Self-report	Baseline and 12, 24, and 36 mo
	HIV and cancer stigma (AYA living with HIV)	Anticipated stigma measures [71,72]	Self-report	Baseline and 12, 24, and 36 mo
	Cancer risk (AYA living with HIV)	Updated Research Triangle Institute cancer survey	Self-report	Baseline and 12, 24, and 36 mo
	Group education and sessions (AYA living with HIV)	Number and proportion of education sessions attended (dose)	PC tool; study database	12, 24, and 36 mo
	One-on-one education (AYA living with HIV)	Number of women receiving each level of strategy (dose)	PC tool; study database	12, 24, and 36 mo
	HIV and cancer team training (health care provider)	Proportion who attended initial training sessions (dose)	PC tool; study database	12, 24, and 36 mo
	Network meetings (health care provider)	Number and proportion of meetings attended (dose)	PC tool; study database	12, 24, and 36 mo
	Clinical team knowledge, confidence in ability, and collaboration (health care providers)	Survey on skills and patient communication; stigma related to AYA living with HIV (modified Nyblade instrument [73]) and peer learning and coordination	Self-report	Baseline and annually
	Diagnostic procedures by cancer type	Number of supplemental and diagnostic tests conducted	Clinical record	12, 24, and 36 mo
	Treatment modality by cancer type	Chemotherapy sessions; surgery; type of radiation	Clinical record	12, 24, and 36 mo

^a^KS: Kaposi sarcoma.

^b^NHL: non-Hodgkin lymphoma.

^c^CC: cervical cancer.

^d^PC: peer counselor.

^e^CD4: cluster of differentiation 4.

^f^Among AYA living with HIV and diagnosed with cancer.

^g^NHL stage based on the Lugano classification, CC stage based on the International Federation of Gynecology and Obstetrics, and KS stage based on the AIDS Clinical Trial Group system.

^h^AYA: adolescents and young adults.

^i^ART: antiretroviral therapy.

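### The recurrence end point counts followed patients whose cancer never cleared the same as patients in lasting remission, so it can hide a benefit of ARROW or make it look worse

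*Protocol article*

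**What the plan says.** The protocol article defines the end point in two places. Under Study End Points, Cancer Treatment Cohort, "the tertiary end point is the proportion with recurrence at 24 and 36 months (among those with 24- and 36-month follow-up". In Table 2, the specification for recurrent disease is patients "living with HIV and cancer who experience cancer recurrence", and the footnote to that row gives the population: "Among AYA living with HIV and diagnosed with cancer". The Data Collection section sends the reader to Table 2 for end point definitions. Neither place makes remission a condition or says how persistent or progressive cancer is classed.

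The primary end point of this cohort is adherence, defined as "complete all treatment modalities as prescribed; 2-week delays will be allowed" and assessed 12 months after diagnosis. For planning, "the estimated current level of adherence is 75%, which will increase to at least 90% with the ARROW program" (Sample Size and Recruitment, Cancer Treatment Cohort).

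**The concern.** Take three patients, all alive and seen at month 24. One was disease-free after treatment and has relapsed: an event. One was disease-free and still is: no event. One left treatment and has cancer that never cleared: on the literal definition also no event, because disease that never went away cannot recur. A poor outcome and the best outcome get the same score.

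This matters here because ARROW is meant to increase the number who complete treatment. If it works, more patients become disease-free and so become able to recur. The proportion with recurrence then mixes two things: how many patients could recur, and how many of those did. Recurrence is also the only cancer outcome beyond 12 months that the end point section lists for this cohort, so a misleading result would stand as the trial's longer-term finding on disease control.

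**Working it through.** **Planning figure.** The sample size "was calculated using conventional specifications (α=.05; 2-sided tests) based on the primary end point", and the article states: "With 50% (250/500) of the patients in each arm, we will have more than 90% power to detect this difference". With 250 per arm, 75% v 90%, two-sided alpha 0.05, the normal-approximation power is 99.4%. Ninety percent power needs 133 per arm (146 with continuity correction). The stated power holds, and 75% and 90% are used below as the planned adherence levels.

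**Model for recurrence as defined.** Let c be the proportion adherent (0.75 control, 0.90 ARROW), rc and rn the probability of becoming disease-free in adherent and non-adherent patients, and qc and qn the probability of relapse once disease-free. Over all followed patients:

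P = c·rc·qc + (1 − c)·rn·qn

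ARROW − control = 0.15 × (rc·qc − rn·qn)

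The difference goes against ARROW only when rc·qc exceeds rn·qn, and cannot then be larger than 0.15·rc·qc.

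**Model with persistent disease counted.** A patient is event-free only if disease-free without relapse:

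C = 1 − [c·rc·(1 − qc) + (1 − c)·rn·(1 − qn)]

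control − ARROW = 0.15 × [rc(1 − qc) − rn(1 − qn)]

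This is never negative, that is, never against ARROW, when rn ≤ rc and qn ≥ qc.

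**Numbers.** The article gives no remission or relapse rates, so rc, rn, qc and qn are assumptions. With rc = 0.80 and qc = 0.25 (rc·qc = 0.20), control v ARROW:

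| Case | rn | qn | Recurrence as defined | Recurrent or persistent | Recurrence among disease-free |
|---|---|---|---|---|---|
| a | 0 | n/a | 15.0% v 18.0% | 55.0% v 46.0% | 25.0% v 25.0% |
| b | 0.20 | 0.50 | 17.5% v 19.0% | 52.5% v 45.0% | 26.9% v 25.7% |
| c | 0.40 | 0.50 | 20.0% v 20.0% | 50.0% v 44.0% | 28.6% v 26.3% |
| d | 0.40 | 0.70 | 22.0% v 20.8% | 52.0% v 44.8% | 31.4% v 27.4% |

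Case a in full. Recurrence: 0.75 × 0.20 = 15.0% v 0.90 × 0.20 = 18.0%. Recurrent or persistent: 1 − 0.75 × 0.60 = 55.0% v 1 − 0.90 × 0.60 = 46.0%.

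As defined, the difference is 3.0 points against ARROW in a, 1.5 against in b, none in c, and 1.2 in favor in d. With persistent disease counted, it is 9.0, 7.5, 6.0 and 7.2 points in favor.

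**Wider range.** A grid of 600 assumption sets (rc 0.6 to 0.9, qc 0.1 to 0.4, rn 0 to 0.5, qn 0.2 to 0.8, with rn ≤ rc and qn ≥ qc) put ARROW worse on recurrence as defined in 380, better in 197 and equal in 23. These counts show that the sign is not fixed. They are not probabilities.

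**The case against.** A reader might infer that success on adherence necessarily makes ARROW look worse on recurrence. The documents do not support that. Suppose every adherent patient becomes disease-free and 20% relapse, while half of non-adherent patients become disease-free and half of those relapse. Recurrence is then 0.75 × 0.20 + 0.25 × 0.25 = 21.25% in control v 0.90 × 0.20 + 0.10 × 0.25 = 20.5% under ARROW, which slightly favors ARROW. A one-directional result follows if relapse is assumed equal in both groups and non-adherent patients reach remission less often, but the article gives no basis for fixing either.

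Three further limits stand. Non-adherence is not abandonment: it includes patients delayed by more than two weeks, many of whom may still become disease-free, so rn = 0 is an extreme case. The calculation applies 75% and 90% to patients followed at 24 months, but patients with persistent cancer who die earlier leave the denominator, which shrinks the group in question and creates a selection problem of its own. And the end point is tertiary: the Analysis of Hypotheses section ties the stated hypotheses to the primary and secondary end points, although it also plans significance testing of this cohort's end points without excluding the tertiary one.

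It can also be said that the article never states in words that persistent disease is scored as no recurrence, and that case rules may sit in an analysis plan not shown here. That carries less weight. The article does state a numerator and a denominator, in the table that it cites for definitions, and followed literally they give this result.

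**Conclusion.** The point holds as a defect of definition. With all followed cancer patients as the denominator and recurrence alone as the numerator, persistent or progressive disease is indistinguishable from lasting remission. Because adherence is expected to differ by 15 points between arms, the measure can hide a real benefit or reverse it.

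The direction of the distortion is unknown. In the four cases worked, a 6.0 to 9.0 point advantage on recurrent or persistent disease shows up on recurrence as anything from 3.0 points against ARROW to 1.2 points in its favor. These sizes rest on assumed remission and relapse rates and on the planned 75% and 90% applying to the patients followed. Severity is minor to moderate: neither the primary end point nor the sample size is affected.

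**What to change.** In both the Study End Points section and Table 2, class each patient at 24 and 36 months as disease-free, recurrent, persistent or progressive, or dead. Report recurrent, persistent or progressive cancer as the end point, with death either shown as its own category or included in the composite, and say which. Without a rule for death, a patient who dies with persistent cancer before month 24 still drops out of the measure.

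Recurrence alone can be kept as a descriptive figure among patients documented disease-free, beside the proportion who reached that state. It should not be the main comparison, because that subset is formed after randomization. The same edit should align the timing: Table 2 lists recurrence at 36 months only, the end point section at 24 and 36.

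The cost is a wording change and one more category in the abstraction of hospital records that is already planned. Only 105 of the planned 500 patients had been enrolled by March 2025. The drawback is that disease status may be unknown for some patients who left treatment. The number unknown should be reported by arm.

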**HIV status, demographics, mediating outcomes, intervention dose, and clinical services**				
	HIV status and diagnosis date	Perinatally or behaviorally infected; CD4 count	Clinic record	Baseline
	Demographics and socioeconomic status	Research Triangle Institute AYA Zambia survey	Self-report	Baseline
	Self-efficacy (AYA living with HIV)	Generalized self-efficacy Scale [69]	Self-report	Baseline and 12, 24, and 36 mo
	Social support and mental health (AYA living with HIV)	Brief social support and patient health questionnaires [69,70]	Self-report	Baseline and 12, 24, and 36 mo
	HIV and cancer stigma (AYA living with HIV)	Anticipated stigma measures [71,72]	Self-report	Baseline and 12, 24, and 36 mo
	Cancer risk (AYA living with HIV)	Updated Research Triangle Institute cancer survey	Self-report	Baseline and 12, 24, and 36 mo
	Group education and sessions (AYA living with HIV)	Number and proportion of education sessions attended (dose)	PC tool; study database	12, 24, and 36 mo
	One-on-one education (AYA living with HIV)	Number of women receiving each level of strategy (dose)	PC tool; study database	12, 24, and 36 mo
	HIV and cancer team training (health care provider)	Proportion who attended initial training sessions (dose)	PC tool; study database	12, 24, and 36 mo
	Network meetings (health care provider)	Number and proportion of meetings attended (dose)	PC tool; study database	12, 24, and 36 mo
	Clinical team knowledge, confidence in ability, and collaboration (health care providers)	Survey on skills and patient communication; stigma related to AYA living with HIV (modified Nyblade instrument [73]) and peer learning and coordination	Self-report	Baseline and annually
	Diagnostic procedures by cancer type	Number of supplemental and diagnostic tests conducted	Clinical record	12, 24, and 36 mo
	Treatment modality by cancer type	Chemotherapy sessions; surgery; type of radiation	Clinical record	12, 24, and 36 mo

^a^KS: Kaposi sarcoma.

^b^NHL: non-Hodgkin lymphoma.

^c^CC: cervical cancer.

^d^PC: peer counselor.

^e^CD4: cluster of differentiation 4.

^f^Among AYA living with HIV and diagnosed with cancer.

^g^NHL stage based on the Lugano classification, CC stage based on the International Federation of Gynecology and Obstetrics, and KS stage based on the AIDS Clinical Trial Group system.

^h^AYA: adolescents and young adults.

^i^ART: antiretroviral therapy.

### Analysis of Hypotheses

We will use an intent-to-treat approach to test the hypotheses (related to the dual primary and secondary end points) that AYA living HIV in the ARROW program, compared with those receiving one-time education, will have higher uptake of early diagnostic services, increased adherence to treatment, and improved outcomes.

For the facilities assigned to the intervention group in the early detection cohort, we will examine the effects at the individual level across the 2 randomization groups. Given the need to consider the influence of the cluster randomization, we will use generalized estimating equation models to estimate the effect across the trial arms. If the Hausman assumption of correlation between the random and fixed effects is violated, then we will include fixed effects representing cluster identification [74]. For the cancer treatment cohort, we will generate summary statistics for the end points and test statistical significance. We will also conduct logistic regressions to identify key factors that predict adherence.

For both trials, we will adjust for baseline covariates, including sociodemographic factors, should the initial descriptive analyses suggest differences in the distribution of these factors across the study arms. We will also explore the use of propensity scores to control for systematic differences between the AYA living with HIV in the 2 trial arms. In further analyses, we will compare differences in mediating outcomes across the randomized groups and examine the potential moderating roles of key individual behavioral and social factors hypothesized to influence adherence along the cancer care continuum (eg, social support, stigma, and self-efficacy), as shown in Figure 1. We will test the “dose” of the ARROW program received as a covariate in these models. In additional analysis, we will explore differences in the end points by age groups and type of cancer, as appropriate. We will also assess whether knowledge, self-efficacy, social support, and stigma differ by age groups and among AYA living HIV, both with and without cancer.

For measures where we have baseline and 12-, 24-, and 36-month data (eg, self-efficacy and stigma), we will perform difference-in-difference analysis, which will allow for comparisons over time and across the study arms. To understand potential variation across the HIV treatment facilities, we will conduct comparisons to analyze differences in mediating outcomes for the AYA living with HIV and the study end points. Furthermore, to understand ARROW program’s impact on health care providers, we will assess dose of the intervention (network session attendance) and change in knowledge, confidence in ability to care for AYA living with HIV, and peer collaboration.

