##### Early Detection Cohort

We propose a cluster randomized study to be implemented at 18 HIV treatment facilities in Lusaka province. Three facilities serving each type of regional population (urban, periurban, or rural populations) will be randomly assigned to a study arm: the ARROW program or one-time education. Overall, 9 (50%) facilities will be assigned to each arm of the trial, with data collection at baseline and at 12-, 24-, and 36-month follow-up. At each of the 18 clinics, we will enroll 100 men and 100 females resulting in a total of 3600 participants in the early detection cohort. The 200 AYA living with HIV per facility will be selected by first reviewing the HIV register and identifying those who meet the study inclusion criteria: 15 to 39 years of age, on ART for at least 6 months, not pregnant, and with no pending plans to move from the current residence during the 3-year study duration. For all the 3600 participants, we will collect baseline data and capture information on study end points from the SmartCare system, and the supplemental data will be collected by PCs and trained study data collectors (eg, tracking referrals for all participants and obtaining results of biopsies).

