#### Sample Size and Recruitment

##### Early Detection Cohort

We will use stratified random sampling to select an equal number of male and female participants and a mix of AYA living with HIV with perinatally and behaviorally acquired HIV. In terms of age distribution, 20% (720/3600) of the sample will be aged 15 to 19 years, 20% (720/3600) will be aged 20 to 24 years, and 60% (2160/3600) will be aged 25 to 39 years. We will oversample AYA living with HIV in each stratum to account for AYA living with HIV who may not meet inclusion criteria or who decline to participate. HIV facility staff will contact AYA living with HIV or consenting adults (for those aged 15 to 17 years) to discuss the study, and those interested will meet with trained data collectors who will assess eligibility and obtain consent or assent. The sample size was calculated assuming conventional specifications (α=.025 for each end point, 2-sided tests) based on the dual primary end points and allowing for the detection of an absolute 20% point improvement in the primary end points, which is our minimum threshold to consider the ARROW program successful. For the one-time education arm, given the current low level of uptake of early diagnosis services, we estimate uptake of physical examinations to be about 15% (15/100) and CC screening to be about 20% (20/100) at 12 months. With our proposed sample size of 3600, we will be able to detect a 20% difference in uptake of physician examination (35% in the ARROW arm) with over 90% power and CC screening (40% in the ARROW arm) with over 85% power. We can achieve this even after accounting for up to 10% attrition at 12 months (a previous study conducted by the research team achieved this retention rate without the level of active participant contact planned for this study) [67]. We estimate that the interclass correlation coefficient will be in the range of 0.03 to 0.05 because correlation coefficients for binary data are typically quite small, especially when physical examinations and screening uptake are very low [68].

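### The facility fixed-effects fallback for the early detection cohort cannot estimate the arm effect, because whole facilities are allocated to arms

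*Protocol article*

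**What the plan says.** Under Overall Study Design, Early Detection Cohort, the unit of allocation is the facility: "Three facilities serving each type of regional population (urban, periurban, or rural populations) will be randomly assigned to a study arm", and "Overall, 9 (50%) facilities will be assigned to each arm of the trial". On facility size, "we will enroll 100 men and 100 females resulting in a total of 3600 participants in the early detection cohort".

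Under Analysis of Hypotheses, "we will use generalized estimating equation models to estimate the effect across the trial arms". The next sentence sets the fallback: "If the Hausman assumption of correlation between the random and fixed effects is violated, then we will include fixed effects representing cluster identification". Nothing restricts it to secondary analyses. It sits in the section that tests the dual primary end points.

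Under Sample Size and Recruitment, Early Detection Cohort, the test level is "α=.025 for each end point, 2-sided tests", and for the comparison arm "we estimate uptake of physical examinations to be about 15% (15/100) and CC screening to be about 20% (20/100) at 12 months". The same section gives a 20-point target difference, an ICC of 0.03 to 0.05, up to 10% attrition, and power above 90% (examination) and above 85% (cervical cancer screening). The article names no GEE variance estimator, reference distribution or degrees of freedom.

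**The concern.** In a trial that randomises facilities, all information on the arm effect lies between facilities. Facility fixed effects remove exactly that information. A rule that adds them to the primary model therefore removes the quantity the trial was set up to estimate.

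At stake is the prespecification of the primary analysis. If the rule triggers, the named branch yields no arm estimate or an arbitrary one, and the team must choose another analysis with the data in hand.

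A second, smaller matter is the method the fallback would replace. With only nine facilities per arm, GEE in its common default form is known to reject too often, and the article does not say how this is handled.

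**Working it through.** **1. Can the fallback estimate the arm effect?**

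Inputs: 18 facilities, nine per arm, arm constant within facility (Overall Study Design).

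- Let F1 to F18 be the facility indicators, with F10 to F18 in the ARROW arm. Then arm = F10 + F11 + … + F18 for every participant.
- The design matrix with 18 facility columns plus arm has 18 + 1 = 19 columns. Its rank, checked numerically, is 18. The arm coefficient is not estimable, whatever the ICC or uptake.
- If arm is forced to stay alongside an intercept, two facility columns must go, one from each arm. With both from the same arm, the rank falls to 17. The arm coefficient is then the contrast between those two facilities alone, and there are 9 × 9 = 81 such pairs.
- How much that contrast could vary with no true effect (15% uptake, ICC 0.05, 180 per facility after 10% attrition): the variance of one facility's proportion is 0.15 × 0.85 × (0.05 + 0.95/180) = 0.00705. The SD of a two-facility difference is √(2 × 0.00705) = 0.119, or 11.9 percentage points. For nine against nine it is 0.119/√9 = 0.040, or 4.0 points. The target is 20 points.

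**2. Do repeated measurements rescue it?**

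The examination and screening end point is one proportion at 12 months (Study End Points). Table 2 lists it at 12, 24 and 36 months, with no baseline timing. All of these follow randomisation, so facility effects still absorb the arm main effect. Facility effects could leave an arm-by-time change estimable, but Analysis of Hypotheses plans difference-in-difference only for measures with baseline data, with self-efficacy and stigma as examples.

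**3. Is the trigger suitable?**

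- A Hausman test compares a random-effects with a fixed-effects estimator. GEE has no random effects.
- The fixed-effects fit supplies no arm coefficient, so any comparison must rest on covariates that vary within a facility, such as age or sex. It says nothing about arm.
- The random-effects assumption is the absence of correlation between cluster effects and covariates. The sentence makes correlation the assumption, so read literally it adds fixed effects when there is none.

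**4. Stated power, reproduced**

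Inputs: α = 0.025 two-sided; ICC 0.05 (worst case); 10% attrition, so m = 180 per facility for examination and 90 women for screening. Design effect = 1 + (m − 1) × ICC; effective n per arm = 9m / design effect.

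| | Examination, 15% v 35% | Screening, 20% v 40% |
|---|---|---|
| Design effect | 1 + 179 × 0.05 = 9.95 | 1 + 89 × 0.05 = 5.45 |
| Effective n per arm | 1620/9.95 = 162.8 | 810/5.45 = 148.6 |
| SE of difference | √(0.355/162.8) = 0.0467 | √(0.400/148.6) = 0.0519 |
| 0.20/SE | 4.28 | 3.86 |
| Power, normal | 97.6% | 94.0% |
| Power, t on 16 df (critical value 2.473) | 95.5% | 90.4% |
| Power, t on 14 df (critical value 2.510) | 95.0% | 89.6% |

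The stated figures hold as lower bounds in every row. The normal row uses the pooled variance under the null. The 14 df row allows for two region terms (18 − 4 = 14).

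**5. False-positive rate of GEE at nominal 2.5%, by variance method**

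Null beta-binomial simulation, nine v nine facilities of equal size, ICC 0.03 and 0.05, m = 180 at 15% and m = 90 at 20%; 200,000 runs per setting, or 20,000 where region terms are added.

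| Method | Rejection rate |
|---|---|
| Uncorrected sandwich, normal reference | 5.0–5.4% |
| The same, with region terms | 6.7–7.1% |
| Uncorrected sandwich, t on 16 df | 3.3–3.6% |
| Kauermann-Carroll-type correction, t on 16 df | 2.5–2.7% |
| Mancl-DeRouen-type correction, t on 16 df | 1.8–2.0% |
| Facility-level t test, 16 df | 2.4–2.5% |

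Analytic check of the top row (identity link): 2 × P(t16 > 2.2414 × √(8/9)) = 2 × P(t16 > 2.113) = 5.06%.

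**The case against.** **The fallback is conditional, and its failure would be noticed.** The chance of triggering is unknown. A dropped term would be evident on fitting, and the GEE estimate could still be computed. The sentence also cites a source that is not at hand, so the exact procedure intended cannot be checked. This stands against saying that the trial would have no answer, which a reader might infer. It does not save the rule: a prespecified branch that must be abandoned when reached leaves the primary analysis to a post hoc choice.

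**Such detail belongs in the analysis plan.** This does not help the fallback, because the article states a specific rule and that rule is wrong. An analysis plan that follows it inherits the defect, and one that departs from it contradicts the published protocol.

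The argument does hold for the GEE variance method. A reader might infer that the 2.5% tests really run at 5%. The article names no uncorrected sandwich and no normal reference, and an analysis plan not shown may specify a correction. A reader might also infer a family error near 10%. That would need nearly independent tests as well; with strong correlation it would stay near 5%. Moreover, the two outcomes simulated both belong to the first primary end point, and the second was not examined. Neither inference is supported.

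**The choice of correction is partly preference.** Agreed: several methods are acceptable, and 16 df is not the only defensible reference given allocation within three region types.

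**Conclusion.** The fallback is wrong as written. It follows by algebra from facility-level allocation that facility fixed effects absorb arm (19 columns, rank 18), with no assumption about ICC, uptake or software. The Hausman trigger does not fit GEE, carries no information about arm, and is worded backwards. The consequence is an unusable branch of the primary analysis for the early detection cohort.

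The small-sample point is conditional. If an uncorrected sandwich with a normal reference were used, the rejection rate would be about 5% for a nominal 2.5%. That figure assumes beta-binomial outcomes, equal facility sizes, ICC 0.03 to 0.05 and no region terms; unequal sizes were not simulated. It is a reason to name the method, not evidence that the planned tests are invalid. The stated power is not in question.

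**What to change.** Before the 12-month arm comparison is run:

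1. Delete the Hausman sentence and the facility fixed-effects fallback.
2. Keep GEE clustered by facility as the sole primary analysis. If an adjustment for the allocation strata is wanted, use region type, which leaves arm estimable because both arms occur in each region.
3. Unless the analysis plan already does so, name a small-sample-corrected variance (for example Kauermann-Carroll or Fay-Graubard) with a t reference on between-facility degrees of freedom: 16, or 14 with two region terms. A facility-level summary analysis can serve as a check.

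The cost is a change of wording and a software option, with no new participants or data. Confidence intervals become somewhat wider: the critical value rises from 2.241 to 2.473 on 16 df, and a corrected standard error adds a little more. Power at ICC 0.05 with 10% attrition remains about 95% and 90%, above the stated 90% and 85%.
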